## Abstract

**Background:**

The Unified Protocol (UP) is a transdiagnostic intervention based on emotional regulation for the treatment of emotional disorders. Its application in individual and group formats has been studied worldwide, obtaining similar results to specific protocols but with a lower drop-out rate and improving the cost–benefit ratio, since a larger number of patients can benefit from it. Moreover, the inclusion of digital technologies in psychotherapy aims to improve the accessibility of treatments, especially since the pandemic of COVID-19 that forced the implementation of treatments through teletherapy increasing its use. To date, no studies have been carried out in Argentina on the application of the UP in a group format and through teletherapy. The aim of the present study is to evaluate the efficacy of the UP in a group format and through teletherapy in the Argentine population.

**Methods:**

A parallel-group, controlled, randomized trial, with pre-post and repeated follow-up measures intergroup design will be conducted. One hundred eighty patients will be randomized to one of the following conditions: an online, group-based UP intervention or a waiting list. The Beck Depression Inventory-II and the Beck Anxiety Inventory will be used to compare primary outcomes and the Beck Hopelessness Scale, Difficulties in Emotion Regulation Scale, Positive Affect and Negative Affect Scale, and Multicultural Quality of Life Index will be administered for secondary outcomes at baseline, post-intervention, and 3 months follow-up. Ad-hoc questionnaires will be used to assess patients’ experiences and treatment satisfaction.

**Discussion:**

The purpose of this trial is to evaluate the efficacy of the online and group application of the UP in the Argentine population, as well as to evaluate the patient’s experience and satisfaction with the treatment. It is expected that the findings of this study will be useful in reducing anxious and depressive symptomatology, will allow us to adapt the UP to our culture, and will improve accessibility to treatment.

**Trial registration:**

ClinicalTrials.gov NCT05275322. Registered on 11 March 2022.

## Introduction

### Background and rationale {6a}

Research has established emotional disorders as the mental disorders with the highest prevalence worldwide [1]. In Argentina, the prevalence of anxiety disorders has been estimated at 16.4%, and depression at 8.7%, placing them as the most prevalent disorders among our population [2]. These disorders are highly comorbid to each other and recently have been defined under the umbrella of emotional disorders (ED), as they share common etiological and maintaining mechanisms [3].

These disorders involve significant economic costs for public health given their high prevalence and chronicity. Moreover, access to evidence-based treatments in Argentina is often difficult given the lack of therapists trained in their application [4]. The first-choice treatment recommended by the National Institute for Health and Care Excellence (NICE) for ED is cognitive-behavioral therapy [5]. The Unified Protocol is a transdiagnostic approach focused on common aspects of ED [6] that has shown equivalent efficacy to specific CBT protocols for different disorders across the depressive and anxious spectrum [7].

Given the huge gap in access to treatments, the use of technology in mental health and psychological therapy is expected to increase access to effective treatments in populations that do not have access to these treatments. During the last few years, the application of teletherapy in different disorders has been studied and similar outcomes to face-to-face treatments have been obtained [8–10]. In addition, besides the benefits of the inclusion of digital technologies, group treatments also facilitate greater access to treatments as they offer superior cost-effectiveness [11], which is especially relevant in our population.

The application of the UP in group and face-to-face formats has been studied around the world [12–15], and recently, its online application has begun to be studied in pilot studies [16–18]. In Argentina, its application has been studied in a pilot way in a face-to-face and group format [19] and in a group and online format [20]. To date, this will be the first randomized controlled trial of the Unified Protocol in Argentina.

### Objectives {7}

The aim of the present study is to evaluate the efficacy of the UP in online and group format in the Argentine population. For this purpose, the following research questions have been formulated:Will the Unified Protocol delivered in an online and group format be more effective than the absence of treatment (control group) for anxiety and depressive disorders in the Argentine population?What are the experiences of patients in online and group therapy?

### Trial design {8}

This is the protocol of a parallel-group, controlled, randomized trial, with a pre-post and repeated follow-up measures intergroup design. This trial is framed in the superiority framework.

A two-arm trial is going to be carried out. For this reason, a waiting list has been chosen as a comparator. Participants with low to moderate anxiety/depressive symptoms will be randomly assigned to Group 1: Unified Protocol for Transdiagnostic Treatment of Emotional Disorders (UP) intervention, or Group 2: Wait-List Control group.

The assessment will be conducted at three-time points for Group 1: an initial assessment before being randomized (pretreatment; T0), at the end of the intervention (post-treatment; T1), and 3 months after the completion of the intervention (T2). Group 2 will be assessed on T0 and T1. T2 would not be measured in this group since after T1 they will start treatment.

CONSORT patient’s flowchart is presented in Fig. 1.

**Fig. 1 Fig1:**
[figure not shown]
CONSORT flow diagram

## Methods: participants, interventions, and outcomes

### Study setting {9}

Our research team will conduct this study at the University of Buenos Aires, in Buenos Aires (Argentina), and will be delivered entirely online.

### Eligibility criteria {10}

To participate in this study, participants must fulfill the following inclusion criteria: (1) ≥ 18 years old; (2) submit informed consent; (3) agree to participate in all the scheduled sessions; (4) agree to have the sessions recorded (both audio and video) for monitoring purposes; (5) meet criteria for a primary diagnosis of an anxiety disorder (e.g., panic disorder; agoraphobia; social anxiety disorder; generalized anxiety disorder; unspecified anxiety disorder), or unipolar depression (major depressive disorder; dysthymia) according to DSM-5; (6) not being currently receiving other psychological treatment.

Exclusion criteria will be the following: (1) comorbidity with bipolar disorder, obsessive–compulsive disorder, post-traumatic stress disorder, psychotic disorders, bipolar disorder, eating disorders, borderline personality disorder, substance abuse disorder; (2) presence of suicidal plans and/or acts or having had suicidal plans and/or acts in the last 12 months; (3) having a suicidal ideation score on the Beck Hopelessness Scale (BHS) ≥ 10; (4) being currently receiving psychological treatment or have received psychological treatment within the last year.

All candidates who are not included in the study will be informed of this decision and will be given information on places to seek free treatment.

### Who will take informed consent? {26a}

At the initial screening, participants will receive informed consent from the therapist and will have the opportunity to ask questions about their participation. After that, they will receive the informed consent form and will have to sign it online.

### Additional consent provisions for collection and use of participant data and biological specimens {26b}

In this study, biological samples will not be collected. Participant data will be used only for the research proposes.

### Interventions

#### Explanation for the choice of comparators {6b}

The present study aims to evaluate the efficacy of the application of the Unified Protocol in a group and online format in the Argentinean population. A two-arm trial is going to be carried out. For this reason, a waiting list has been chosen as a comparator.

#### Intervention description {11a}

## Unified Protocol

The UP focuses on different strategies of emotion regulation to address neuroticism, a common factor in all emotional disorders (ED). This intervention intends to address dysfunctional emotional regulation strategies in participants and encourages the use of more adaptive strategies to promote tolerance to intense negative emotions. Participants will receive online, synchronous group therapy based on the UP model for 10 subsequent weeks, with a duration of 90 min for each meeting. After every session, they will receive the chapter of the UP’s Spanish patient’s workbook [6] with the notions addressed in the session and the indications to practice during the week.

Contents of each session:Session 1:

Coordinators’ and participants’ introductions. Session framework. Introduction to the approach and ED. Conceptualization of ED and identification of their own intense emotions, aversive reactions, and avoidance efforts.Session 2:

Module 1: Motivation for change and commitment to treatment. Describing issues, goals, and steps to accomplish them. Introduction to change motivation. Decision balance exercise.Session 3:

Module 2: Understanding emotions. Introduction to the topic of this session (psychoeducation of emotions). Presentation of the three-component model and introduction to the concept of Emotion-Driven Behaviors (EDBs), as well as the antecedents and consequences of emotional experiences.Session 4:

Module 3: Emotional awareness training. Introduction to mindfulness. Non-judgment emotional awareness exercises will be carried out during the session, and participants will receive afterwards by email with the taped audio so as to do it during the week. Introduction to emotional induction and practicing mindfulness when facing stimuli that trigger emotions (videos/audio). Introduction to anchoring in the present.Session 5:

Module 5: Cognitive flexibility. Introduction to cognitive flexibility. Ambiguous image exercise. Introduction to mind traps and cognitive re-evaluation exercise during the session.Session 6:

Module 5: Emotional avoidance and EDBs. Introduction to emotional behaviors. Introduction to EDBs and avoidance types. A cognitive suppression exercise will be carried out during the session. Working with alternative actions.Session 7:

Module 6: Physical sensations tolerance. Introduction to interoceptive exposure. Interoceptive exposure exercises during the session: hyperventilating, running on the spot, jumping, breathing through a straw, and twirling.Sessions 8 and 9:

Module 7: Emotional exposure. Introduction to the exposure to intense emotions. Building the exposure hierarchy. Introduction to the emotional exposure form.Session 10:

Module 8: Maintenance of treatment gains and relapse prevention. Introduction to relapse prevention and plans for future practice. Closure and group farewell among therapists and participants.

### Wait-List Control

Participants in the waiting list control will receive the same intervention as described above after the end of the group intervention. Participants on the waiting list will complete the same assessments as the intervention group (T0, T1), except the last one (T2).

### Criteria for discontinuing or modifying allocated interventions {11b}

In this study, the criteria for discontinuing the intervention will be (1) participants who fail to attend two or more sessions, (2) participants who have current suicidal plans or acts, and (3) participants who request to withdraw from the trial.

Participants who have current suicidal plans or acts will be withdrawn from the trial and will receive individual care.

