### Relevant concomitant care permitted or prohibited during the trial {11d}

In this trial, participants who receive another psychological intervention during their participation in the study will be excluded. Psychopharmacological interventions are permitted with the regard that the dose dosage remains stable during the trial.

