#### Sample size {14}

The sample size has been estimated based on a meta-analysis of previous studies of the application of the Unified Protocol in emotional disorders compared to a control group [21]. These studies showed a medium effect size (0.45 g* hedges*) on post-treatment measures. A median effect size (0.5) was assumed to detect differences between the intervention and the control group. G*Power software was used to calculate the sample size. For two groups, with a statistical power of 0.80, and an alpha of 0.05, it is estimated that a total of 150 participants will be required (75 for each condition). Given that previous studies have reported a dropout rate between 15 and 20% [22], the total sample required will be 180 participants, 90 for each group.

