#### Plans to promote participant retention and complete follow-up {18b}

Upon completion of the intervention, participants will be contacted by e-mail and phone calls to encourage them to complete the follow-up.

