#### Methods in analysis to handle protocol non-adherence and any statistical methods to handle missing data {20c}

To address protocol non-adherence, participant education will emphasize the importance of adhering to the protocol, while clear instructions and materials will be provided. Investigators and research staff will receive training and ongoing support. For this, monitoring and supervision procedures will be implemented to detect and correct deviations. Standardization of intervention and data collection procedures across sites will be ensured. Moreover, motivational strategies will be carried out to encourage adherence while barriers to adherence will be identified and addressed.

Missing data will be imputed using the random forest method.

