### Plans for communicating important protocol amendments to relevant parties (e.g., trial participants, ethical committees) {25}

All changes in the protocol must be approved by the University of Buenos Aires. If any changes to the protocol are required during this trial, a new protocol will be designed and submitted to the ethics committee for approval before implementation.

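### Suicidality is a reason to stop the group sessions, but the protocol turns it into removal from the trial, so later outcome scores are lost

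*Protocol article*

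**What the plan says.** Section {11b} of the Protocol article sets out when the allocated intervention is stopped. The second entry in its list reads "2) participants who have current suicidal plans or acts". The sentence after the list goes further: "Participants who have current suicidal plans or acts will be withdrawn from the trial and will receive individual care". The section attaches that consequence to this criterion and not to missed sessions.

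Other sections bear on it:

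- **Eligibility {10}** excludes people with "presence of suicidal plans and/or acts or having had suicidal plans and/or acts in the last 12 months".
- **Trial design {8}** schedules T0, T1 and T2 for the UP arm, and T0 and T1 for the waiting list. It does not mention participants who stop early.
- **Retention {18b}**: "Upon completion of the intervention, participants will be contacted by e-mail and phone calls to encourage them to complete the follow-up".
- **Concomitant care {11d}**: "participants who receive another psychological intervention during their participation in the study will be excluded".
- **Missing data {20c}**: "Missing data will be imputed using the random forest method". It does not say whether withdrawn participants are imputed or left out.

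**The concern.** Two decisions are merged. One is clinical: an acutely suicidal participant should leave an online group and receive individual care. The other concerns data: whether that participant is still assessed at T1 and, in the UP arm, at T2. The first does not require ending the second. Followed as written, the rule ends both.

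The scores lost belong to people who have deteriorated, so the reason they are missing is tied to what the trial measures. The tie is clearest for BDI-II, one of the two primary outcomes. It is less direct for BAI. Eligibility keeps such cases out at entry, so baseline data carry little sign of the later event. An imputation model trained on participants without the event would probably make the missing scores look too good.

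At stake is a bias in the T1 comparison between arms. More cases in UP would flatter the intervention; more in the waiting list would understate its benefit. A case arising after T1 loses only T2, which is measured in UP alone and supports no between-group comparison.

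**Working it through.** The protocol gives no figure for this point, so there is none to reproduce. The check has two parts.

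**1. Does any other section offset the rule?**

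- {8} and the Wait-List Control section give the general schedule, with nothing on assessment after early stopping.
- {11c} provides a phone call after a missed session, which concerns attendance.
- {18b} places follow-up contact at completion of the intervention and does not mention those who stop earlier.
- {11d} points the same way as the rule: individual care could be read as another psychological intervention, which leads to exclusion.
- {20c} imputes what is missing. It does not collect anything.

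None of these restores the scores.

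**2. How large could the effect be?**

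Inputs from Sample size {14}: 90 per arm, 180 in total, planned standardised effect 0.5. For attrition, "previous studies have reported a dropout rate between 15 and 20" per cent.

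Assumed, because the documents give neither:

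- a difference of one or two cases between arms;
- a true T1 score worse by *s* = 0.5 to 2 SD than the imputed value or, if the case is dropped, than the mean of those remaining.

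For one arm of *n* with *k* such cases:

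- Dropped: the full mean is [(n − k)m + k(m + s)]/n = m + ks/n, where m is the mean of those remaining, so the error is ks/n.
- Imputed: each of the k values is wrong by s, so the error in the mean is again ks/n.

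The two agree because of how *s* is defined, so the agreement is not evidence about *s*. The shift in the contrast is therefore (k_UP − k_WL)/90 × s:

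| Difference in cases | s = 0.5 SD | s = 2 SD |
|---|---|---|
| 0 | 0 | 0 |
| 1 | 1/90 × 0.5 = 0.0056 | 1/90 × 2 = 0.0222 |
| 2 | 2/90 × 0.5 = 0.0111 | 2/90 × 2 = 0.0444 |

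- Against the planned effect: 0.0056/0.5 = 1.1%; 0.0444/0.5 = 8.9%.
- Against sampling error: SE = √(2/90) = 0.149; 0.0056/0.149 = 0.04; 0.0444/0.149 = 0.30.
- Share of expected dropout: 0.15 × 180 = 27 and 0.20 × 180 = 36, so one to two cases are 1/36 = 2.8% to 2/27 = 7.4%.

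A harsher assumption, with 5% of UP withdrawn, none from the waiting list and *s* = 2 SD, gives 0.05 × 2 = 0.10 SD. The eligibility exclusion makes that unlikely.

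**The case against.** The strongest reply is that this is mostly an omission. Rules for assessing and analysing people who leave early often sit in a full protocol or SAP, and neither is shown. The wording may also be loose: the same list treats a request to leave the trial as a reason to stop the intervention, so the section does not cleanly separate the two levels. The retention sentence does not say that contact is limited to completers, and completion could mean the end of the intervention period. The trigger is suicidality, not a score, and its link to BAI is not shown. Finally, the illustrated effect is small, rests on assumed inputs, and is only partly recoverable.

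Much of this stands. The retention sentence is weak support, the BAI link should be held loosely, and the size is small. The silence of {20c} on withdrawn participants is not itself a fault here.

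The core is not an omission, though. The article states a rule, removal from the trial, and its natural reading ends assessment. A SAP governs the analysis of collected data and cannot supply questionnaires that were never given. A full protocol could add assessment after withdrawal, but it would then have to qualify the sentence printed here. Moving these participants to individual care is right and is not in dispute.

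**Conclusion.** The point holds and is minor. The protocol converts a reason for stopping treatment into an end to trial participation, for a reason related to outcome, and nothing in the article offsets it.

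Under the assumptions above, the T1 contrast moves by 0.006 to 0.044 SD, or 0.04 to 0.30 of a standard error. The direction is unknown, because it depends on which arm has more cases, and equal numbers give about zero. Case numbers and score shifts are assumed; the documents supply neither. T2 loss does not affect any between-group comparison. The point is unlikely to change the trial's conclusion. It is worth correcting because the wording change is simple and keeps information on the participants who fared worst.

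**What to change.** - In {11b}, replace removal from the trial with *discontinued from the group intervention and given individual care*.
- Offer these participants the scheduled T1 questionnaires and, in the UP arm, T2, with their consent and when the treating clinician judges it safe.
- State in {11d} that this individual care does not lead to exclusion. Once these participants stay in the study, that sentence is needed to avoid a conflict.
- Analyse them in the arm to which they were randomised and report their number by arm.

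**Cost.** Under {25}, a change means that "a new protocol will be designed and submitted to the ethics committee for approval before implementation". The amendment would include a safety judgement on contacting these participants. The questionnaires and time points are already scheduled.

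**Limits.** Some participants will refuse. T1 scores taken after transfer partly reflect the individual care, so the fix recovers less than the full shift shown above. With recruitment running from April 2022 to an expected December 2023 (Trial status), it reaches only participants still to be assessed.

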### Strategies to improve adherence to interventions {11c}

The therapists will encourage the importance of attending scheduled sessions and completing the exercises learned between sessions. After each session, an email will be sent to remind this. If a participant is absent from one session, a member of the research group will contact him/her by phone.

### Relevant concomitant care permitted or prohibited during the trial {11d}

In this trial, participants who receive another psychological intervention during their participation in the study will be excluded. Psychopharmacological interventions are permitted with the regard that the dose dosage remains stable during the trial.

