## Assignment of interventions: blinding

### Who will be blinded {17a}

Due to the nature of this intervention, treatment allocation cannot be blinded to the therapist or participants. Participants will not receive details about the research aims.

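### Two rules remove randomised participants for post-randomisation events, which leaves the T1 comparison open to bias of unknown size and direction

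*Protocol article*

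**What the plan says.** Two sentences in the protocol article remove people after randomisation. Under concomitant care {11d}, "participants who receive another psychological intervention during their participation in the study will be excluded". Under the discontinuation criteria {11b}, "Participants who have current suicidal plans or acts will be withdrawn from the trial and will receive individual care".

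The same {11b} list names "participants who fail to attend two or more sessions", but as a criterion for discontinuing the intervention.

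The arms differ in contact up to T1. In the UP arm, "Participants will receive online, synchronous group therapy based on the UP model for 10 subsequent weeks", and "If a participant is absent from one session, a member of the research group will contact him/her by phone". For the other arm, "Participants in the waiting list control will receive the same intervention as described above after the end of the group intervention". The section on blinding {17a} says that "treatment allocation cannot be blinded to the therapist or participants".

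The section on non-adherence and missing data {20c} lists education, training, supervision and motivation, followed by one sentence that prescribes random forest imputation. On retention, {18b} says: "Upon completion of the intervention, participants will be contacted by e-mail and phone calls to encourage them to complete the follow-up".

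**The concern.** A superiority claim rests on comparing the groups as randomised. When someone leaves the comparison because of an event after allocation, the groups that remain can differ for reasons other than the treatment.

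Both removal rules concern such events, and both events plausibly go with higher depression or anxiety scores. The design also gives reason to expect unequal rates. People who know they are waiting untreated have more reason to seek therapy elsewhere. Suicidal plans are more likely to come to light among people whom therapists see every week.

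The article does not say that people removed under these rules still complete T1 or count in their randomised arm. If T1 is not collected, no later analysis decision can bring it back.

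**Working it through.** **Step 1. The three rules side by side.**

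| Event | Consequence in the text | Why the arms may differ before T1 |
|---|---|---|
| Another psychological intervention ({11d}) | Excluded | The waiting arm has more reason to seek it |
| Current suicidal plans or acts ({11b}) | Withdrawn from the trial | More likely to be noticed in the arm seen weekly |
| Two or more missed sessions ({11b}) | Intervention discontinued | Can occur only in the UP arm |

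Only the first two rows state removal from the study. The third supports the point only if those participants also lose their T1 assessment, which the text does not say.

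**Step 2. The plan's own figures.** The plan gives no rate for either exclusion, so there is no figure on this point to reproduce. Its sample-size section {14} supplies the assumed effect (0.5) and 75 participants per arm before dropout. With effect 0.5, two-sided alpha 0.05 (sidedness is not stated; two-sided is assumed) and power 0.80, the standard calculation needs 63 per arm (normal) or 64 (t), not 75. That gap does not affect this point, because a larger sample does not remove selection bias. At 75 per arm, power for 0.5 is 0.86.

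**Step 3. An illustration of size.** Everything in this step is assumed except the effect of 0.5. Let T1 scores have SD 1 with higher scores worse. A share p of an arm is removed through a latent tendency that has correlation r with the T1 score. The mean of those who remain is lowered by r × L(p), where L(p) = φ(z)/(1 − p) and z is the normal quantile at 1 − p:

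- L(0.02) = 0.0484/0.98 = 0.049
- L(0.05) = 0.1031/0.95 = 0.109
- L(0.10) = 0.1755/0.90 = 0.195
- L(0.20) = 0.2800/0.80 = 0.350

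Estimated effect (wait-list minus UP) = 0.5 − r × [L(p wait-list) − L(p UP)].

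| Removed, wait-list / UP | Difference in L | r = 0.3 | r = 0.5 |
|---|---|---|---|
| 5% / 0% | 0.109 | 0.47 | 0.45 |
| 10% / 2% | 0.146 | 0.46 | 0.43 |
| 20% / 5% | 0.241 | 0.43 | 0.38 |
| 2% / 10% | −0.146 | 0.54 | 0.57 |
| 5% / 20% | −0.241 | 0.57 | 0.62 |
| 10% / 10% or 20% / 20% | 0 | 0.50 | 0.50 |

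For example, 20% / 5% with r = 0.5 gives 0.5 − 0.5 × 0.241 = 0.38. With r = 0 every row gives 0.50. A simulation with one million participants per arm agrees to within 0.003. The same shifts, about 0.03 to 0.12 SD in either direction, appear when the true effect is zero.

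**Step 4. Effect on the test at 75 per arm.** A shift of 0.12 SD away from a true zero raises the two-sided type I error from 0.05 to about 0.11. A shift of 0.12 SD against the treatment (0.50 to 0.38) lowers power from 0.86 to about 0.64.

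**Step 5. Does the imputation repair this?** {20c} does not say that it covers excluded or withdrawn participants. If it did, their T1 values would be predicted from people who stayed. That cannot correct loss that depends on the T1 score that was never seen.

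**The case against.** The strongest reply is that the article does not limit the analysis to completers, that analysis sets are commonly defined in a SAP, and that imputation could bring back anyone with T0 but no T1. This stands as far as it goes: the lack of a named analysis set is not the fault here. It does not meet the point, because exclusion and withdrawal are stated rules of conduct, and a SAP cannot recover questionnaires that were never sought.

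Numbers may also be small. The eligibility criteria {10} screen out suicidal plans or acts in the last 12 months and a BHS score of 10 or more, so withdrawals for that reason may be few. That is fair, and no figure in the document settles it.

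Several stronger readings are tempting but unsupported:

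- **Missed sessions end trial participation.** {11b} words this as stopping the intervention and singles out only the suicidality group as leaving the trial.
- **Follow-up is pursued only for those who complete.** The opening words of {18b} can simply mark a time point, and the sentence is not restricted to completers or to one arm.
- **The wait-list has no contact between T0 and T1.** None is described, but a condensed article's silence does not establish that.
- **The UP result is flattered by a known amount.** A reader might multiply the 15 to 20% dropout in {14} by an assumed gap of 0.3 to 0.8 SD, get 0.15 × 0.3 = 0.045 to 0.20 × 0.8 = 0.16 SD, and call this 9 to 32% of 0.5. That dropout is a general rate from previous studies, used to inflate both arms. It is not the rate of removal under these rules, still less in one arm alone.

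**Conclusion.** The point holds in a limited form. Two stated rules take randomised participants out of the study for events that are plausibly related to outcome and plausibly unequal between arms, and nothing in the article keeps these people in the T1 assessment or the comparison. The comparison is open to bias; the document does not show that it is biased.

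Removing worse cases mainly from the wait-list would shrink the estimated effect, and removing them mainly from the UP arm would inflate it. The range of 0.38 to 0.62 around a true 0.5 rests on assumed removal rates of 0 to 20% and correlations of 0.3 to 0.5, with analysis of those who remain. Equal rates with equal dependence, or removal unrelated to outcome, give no bias. The missed-sessions rule needs only a clarification. The clinical handling of participants at risk is not in question.

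**What to change.** Amend the text on data collection and analysis only, leaving clinical management as it is:

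1. State that outside therapy, or stopping the intervention for any reason, does not end outcome assessment. This also clarifies that people who miss sessions stay in follow-up.
2. Seek T1 questionnaires (and T2 in the UP arm) from every randomised participant on schedule, unless consent for data is withdrawn.
3. Include all participants in the primary analysis in their randomised arm.
4. Report outside therapy by arm and use it only in a sensitivity analysis.
5. In {11d}, replace the statement of exclusion accordingly. In {11b}, add that withdrawal does not remove a participant's data or randomised-arm membership from the analysis.

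The cost is a short amendment through the ethics route in {25} and a few more reminders. The effect estimate may change. The change needs no larger sample. It should be made while T1 can still be collected.
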